#### Randomization

Randomization occurred at the school level to avoid contamination between conditions. An independent statistician assigned the participating schools randomly to one of the two conditions: intervention or control. Randomization was carried out using a randomization scheme, stratified by level of education and school size, with the schools as units of randomization.

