### Sample size

#### Power

The power calculation reflects the idea that we want to induce a reduction in the percentage of students engaging in binge drinking (drinking five or more glasses of alcohol on one occasion) at least once during the last four weeks, from the current estimated 50% (among life-time users grade 9/10; estimate based on the results of a national school survey, [1]) to 35%. For a 15% reduction after 12 months among the students in grade 9/10, a sample size of N = 183 in each condition was required to test the hypothesis in a 2-sided test at alpha = 0.05 and a power of (1-beta) = 0.80. Because of the loss of power due to randomization of schools (and not students) and the increase in error because of applying a multiple imputation procedure to fill in missing values, 183*1.4 = 256 respondents per condition (intervention and control) needed to be included at baseline to test the effectiveness of the Dutch Preventure programme.

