### Statistical Analyses

Descriptive analyses will be conducted to examine whether randomization resulted in a balanced distribution of important demographic characteristics and the outcome variables in the two conditions. To control for potential bias, possible confounders will be included in all further analyses.

Analyses will be performed according to the intention-to-treat and completers-only principles, controlling for sex, age, and educational level. Intention-to-treat means that all participants will be analysed in the condition to which they were assigned by randomization. Therefore, missing data at follow up will be imputed using regression imputation. With respect to the completers-only analyses, only the participants with scores on all time points will be included, without the inclusion of imputed data. In both the intention-to-treat and the completers-only analyses, the effects of the intervention condition will be compared with those of the control condition. For continuous outcome measures, t-tests, or Man Whitney U if non-parametric distributions, will be performed. When correction for confounding variables is necessary, multivariate regression analyses will be performed. The fact that the data are clustered, because groups of respondents that are attending the same class and/or school are investigated, will be taken into account in the analyses.

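### The tests named in Statistical Analyses cannot deliver the covariate adjustment and allowance for clustering that the same section promises

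*Protocol article*

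**What the plan says.** All of the analysis statements below come from the Statistical Analyses section of the protocol article.

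- Named tests: "For continuous outcome measures, t-tests, or Man Whitney U if non-parametric distributions, will be performed".
- Regression is conditional: "When correction for confounding variables is necessary, multivariate regression analyses will be performed".
- Adjustment is also unconditional. Both the intention-to-treat and the completers-only analyses are to control for sex, age and educational level, and possible confounders are to enter every analysis after the baseline comparison.
- The section ends by promising that clustering by class and/or school will be allowed for. It names no method.

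The Randomization section fixes the unit: "Randomization occurred at the school level to avoid contamination between conditions". The Recruitment section gives 15 participating schools. The Power section bases the sample size on a yes/no outcome, "the percentage of students engaging in binge drinking (drinking five or more glasses of alcohol on one occasion"), and inflates it by a single factor for school randomisation and imputation together: "183*1.4 = 256 respondents per condition (intervention and control) needed to be included at baseline".

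**The concern.** In their standard form, a two-sample t-test and a Mann-Whitney U take no covariates and treat every student as an independent observation. The three promises in the section (fixed covariates, confounders throughout, clustering) therefore cannot be kept by the only tests it names. Adjustment is stated once as always done and once as done when needed, and no rule says when it is needed. Two analysts could report different results from the same data, and each could claim to have followed the plan.

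This matters more here than in an individually randomised trial. Condition is a property of the school, so any similarity among students of one school feeds directly into the difference between arms. A student-level test that ignores this gives p-values that are too small. The sentence covers whatever is analysed as a continuous score. That could include the drinking-problem index and weekly units among the drinking outcomes, and the depression, anxiety and behaviour scales among the others.

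**Working it through.** **1. Reproduce the plan's own figure.** The inputs from the Power section are 50% against 35%, two-sided alpha 0.05 and power 0.80. The usual two-proportion formula is

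n = [1.960·√(2·0.425·0.575) + 0.842·√(0.50·0.50 + 0.35·0.65)]² / 0.15²,

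which gives 170 per arm, or 183 with the continuity correction. The stated 183 is matched exactly, and 183 × 1.4 = 256.2 agrees with the stated 256. The planned total is 2 × 256 = 512.

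**2. Students per school.** Spreading the 512 target evenly over 15 schools (an assumption) gives m = 512/15 = 34.1.

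**3. Type I error if school is ignored.** The design effect is DE = 1 + (m − 1)·ICC. A nominal 5% student-level test then has true error of about 2·[1 − Φ(1.96/√DE)]. The documents give no ICC, so a range is assumed.

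| Assumed ICC | DE | Type I error | Multiple of 0.05 |
|---|---|---|---|
| 0.005 | 1.166 | 0.0695 | 1.39 |
| 0.01 | 1.331 | 0.0894 | 1.79 |
| 0.02 | 1.663 | 0.1285 | 2.57 |
| 0.03 | 1.994 | 0.1651 | 3.30 |
| 0.05 | 2.657 | 0.2292 | 4.58 |
| 0.10 | 4.313 | 0.3453 | 6.91 |

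**4. The plan's own inflation factor as an anchor.** If all of the 1.4 were design effect, the implied ICC would be 0.4/33.1 = 0.012 and the error 2·[1 − Φ(1.96/√1.4)] = 9.8%. The factor also covers imputation, so the design effect the authors had in mind can be no larger than 1.4. On their own assumption, 9.8% is a ceiling.

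**5. Check by simulation.** There were 4,000 simulated trials per ICC, with 15 schools split 8 to 7, 34 students each and no true effect.

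| ICC | t-test on students | Mann-Whitney on students | t-test on 15 school means |
|---|---|---|---|
| 0 | 4.4% | 4.3% | 4.5% |
| 0.01 | 9.3% | 9.4% | 5.0% |
| 0.02 | 13.0% | 12.2% | 4.7% |
| 0.05 | 22.2% | 21.9% | 5.1% |
| 0.10 | 33.9% | 33.6% | 5.1% |

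The formula and the simulation agree to within about one percentage point. The last column shows that the t-test itself is sound; the problem is its use on individual students. An analysis at school level keeps the nominal error.

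**The case against.** The strongest defence is that the section promises to allow for clustering and the Power section enlarges the sample for school randomisation. An analysis that ignores school is therefore not the plan as written. A reader might infer that the analysis, carried out as stated, inflates the type I error two- to four-fold. The documents do not support that, for two reasons. The inflation arises only if the clustering promise is not kept. And the two- to four-fold range corresponds to ICCs of about 0.013 to 0.040, which the documents do not supply.

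The section also does not say that the t-test is applied to students. Applied to school means it would be valid, although without covariates it would still not meet the adjustment promise. One can further read the unconditional statements as making regression the main analysis and the t-test a simple unadjusted comparison. That reading is possible, but the conditional regression sentence speaks against it, and nothing in the section settles which is meant.

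Two further inferences should not be drawn. The section names no test for a yes/no outcome, and it does not say how a cluster model would be referred to a distribution with so few schools. Both are details that a condensed article commonly leaves to the full protocol or analysis plan, which are not shown. Neither is a defect by itself, and nothing in the text proposes a large-sample normal reference.

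What remains is the conflict between statements that are present. A fuller plan would have to override one of them.

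**Conclusion.** The point holds as an internal contradiction. The named tests, in their standard student-level form, deliver neither the adjustment nor the allowance for clustering that the section commits to, and adjustment is described as both unconditional and conditional.

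The consequence for error rates is conditional. It requires that the tests be run on students with school ignored. The size then depends on an assumed ICC and on an even spread of the 512 target over 15 schools: a modest excess over 5% at an ICC of 0.005, rising to roughly a third of null comparisons at 0.10. If the authors' own inflation factor is taken as the guide, the error would be at most about twice the nominal level. The contradiction should be resolved before the outcome analysis. It does not show that an invalid analysis is planned.

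**What to change.** Replace the t-test/Mann-Whitney sentence and the conditional regression sentence with one stated analysis per outcome type, used in both the intention-to-treat and the completers-only analyses:

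- always adjusted for sex, age and educational level, with any further confounders named in advance;
- always accounting for school, for example by a mixed model or GEE with a school effect, in logistic form for binge and weekly drinking as yes/no;
- with a small-sample correction suited to 15 schools.

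A covariate-adjusted analysis at school level is an equally acceptable choice. The exact model for skewed scores and counts, and the particular small-sample method, can be left to the analysis plan. Whichever is chosen, the degrees of freedom should reflect how the stratification by educational level and school size is handled.

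The cost is a few lines of text, a little more programming, and wider intervals than a student-level test would give. Neither the design nor the data collection changes.

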## Discussion

The present study protocol presents the design of a randomized controlled trial evaluating the effectiveness of a prevention programme called Preventure. The intervention programme aims to prevent adolescents from (problematic) alcohol drinking. It is hypothesized that, after one year of follow-up, students in the intervention condition will be engaging less in binge drinking and weekly drinking, and will have fewer drinking-related problems than those students in the control condition.

### Strengths and limitations

A first strength of Preventure is that it is one of the few school-based programmes with proven effects on drinking behaviour of adolescents [16,20]. Second, the programme is a selective prevention programme. In the field of substance use prevention in The Netherlands, there is a recognized need for selective prevention programmes [13]. Third, the intervention incorporates elements of motivational and cognitive behavioural theory, which have been proven to be effective in reducing alcohol abuse and associated psychological problems. Fourth, Preventure is a short intervention (two sessions), which makes it less time-consuming than regular prevention programmes and therefore easier to implement in schools. A limitation of the study is that the information on the behaviour of the adolescents is based on self-reports, which might lead to measurements errors. However, studies have shown that self-report data of adolescents about their own drinking, smoking, and drug use are generally reliable (e.g. [59,60]).

A general issue with targeted interventions is the selection of participants and providing information to the participants and their parents in an accurate manner. In this study, neither the parents nor the teachers at the school were explicitly informed about the selection variables of the study, to avoid stigmatization of the students. This ethical issue should also be taken into account if the programme is implemented at other schools in the Netherlands in the future.

### Implications for practice

If the Preventure prevention programme is effective, it can be implemented widely in schools in The Netherlands - for example, as part of the Dutch national school prevention programme The Healthy School and Drugs. The Healthy School and Drugs has a large network among institutions for care and treatment of drug addicts and schools.

## Conclusion

This study has described a programme, currently on trial in the Netherlands, for preventing and reducing binge drinking in adolescence. Evaluation of the programme will provide insight into the effectiveness of Preventure in the Netherlands and the precursors of alcohol use among Dutch adolescents.
